# Personalized upper limb training combined with anodal-tDCS for sensorimotor recovery in spastic hemiparesis: study protocol for a randomized controlled trial

**DOI:** 10.1186/s13063-017-2377-6

**Published:** 2018-01-04

**Keywords:** Stroke, Spasticity, Spatial threshold, tDCS, Neurorehabilitation

## Abstract

**Background:**

Recovery of voluntary movement is a main rehabilitation goal. Efforts to identify effective upper limb (UL) interventions after stroke have been unsatisfactory. This study includes personalized impairment-based UL reaching training in virtual reality (VR) combined with non-invasive brain stimulation to enhance motor learning. The approach is guided by limiting reaching training to the angular zone in which active control is preserved (“active control zone”) after identification of a “spasticity zone”. Anodal transcranial direct current stimulation (a-tDCS) is used to facilitate activation of the affected hemisphere and enhance inter-hemispheric balance. The purpose of the study is to investigate the effectiveness of personalized reaching training, with and without a-tDCS, to increase the range of active elbow control and improve UL function.

**Methods:**

This single-blind randomized controlled trial will take place at four academic rehabilitation centers in Canada, India and Israel. The intervention involves 10 days of personalized VR reaching training with both groups receiving the same intensity of treatment. Participants with sub-acute stroke aged 25 to 80 years with elbow spasticity will be randomized to one of three groups: personalized training (reaching within individually determined active control zones) with a-tDCS (group 1) or sham-tDCS (group 2), or non-personalized training (reaching regardless of active control zones) with a-tDCS (group 3). A baseline assessment will be performed at randomization and two follow-up assessments will occur at the end of the intervention and at 1 month post intervention. Main outcomes are elbow-flexor spatial threshold and ratio of spasticity zone to full elbow-extension range. Secondary outcomes include the Modified Ashworth Scale, Fugl-Meyer Assessment, Streamlined Wolf Motor Function Test and UL kinematics during a standardized reach-to-grasp task.

**Discussion:**

This study will provide evidence on the effectiveness of personalized treatment on spasticity and UL motor ability and feasibility of using low-cost interventions in low-to-middle-income countries.

**Trial registration:**

ClinicalTrials.gov, ID: NCT02725853. Initially registered on 12 January 2016.

**Electronic supplementary material:**

The online version of this article (doi:10.1186/s13063-017-2377-6) contains supplementary material, which is available to authorized users.

## Background

Stroke is a leading cause of long-term disability. Up to 85% of patients with sub-acute stroke present chronic upper limb (UL) sensorimotor deficits [1]. While post-stroke UL recovery has been a major focus of attention, efforts to identify effective rehabilitation interventions have been unsatisfactory. This study focuses on the delivery of personalized impairment-based UL training combined with low-cost state-of-the-art technology (non-invasive brain stimulation and commercially available virtual reality, VR) to enhance motor learning, which is becoming more readily available worldwide.

A major impairment following stroke is spasticity, leading to difficulty in daily activities and reduced quality of life [2]. Studies have identified that spasticity relates to disordered motor control due to deficits in the ability of the central nervous system to regulate motoneuronal thresholds through segmental and descending systems [3, 4]. In the healthy nervous system, the motoneuronal threshold is expressed as the “spatial threshold” (ST) or the specific muscle length/joint angle at which the stretch reflex and other proprioceptive reflexes begin to act [5–7]. The range of ST regulation in the intact system is defined by the task-specific ability to activate muscles anywhere within the biomechanical joint range of motion (ROM). However, to relax the muscle completely, ST has to be shifted outside of the biomechanical range [8].

After stroke, the ability to regulate STs is impaired [3] such that the upper angular limit of ST regulation occurs within the biomechanical range of the joint resulting in spasticity (spasticity zone). Thus, resistance to stretch of the relaxed muscle has a spatial aspect in that it occurs within the defined spasticity zone. In other joint ranges, spasticity is not present and normal reciprocal muscle activation can occur (active control zone; [4] Fig. 1). This theory-based intervention investigates whether recovery of voluntary movement is linked to recovery of ST control.

**Fig. 1 Fig1:**
[figure not shown]
Spatial thresholds (STs) in healthy and stroke participants. **a** The tonic stretch reflex threshold (TSRT) can be regulated throughout a range (filled bar) that exceeds the biomechanical range of the joint (open bar). Relaxation and active force can be produced at any angle within the biomechanical range. **b** The intersection of the diagonal line with the zero-velocity line defines the TSRT. In healthy subjects, TSRT lies outside of the biomechanical range of the joint (arrow) during the relaxed state. **c** In patients with stroke, TSRT may lie within the biomechanical range in the relaxed state, defining the joint angle at which spasticity begins to appear (spasticity zone). In the other joint ranges, spasticity is not present (active zone)

We also consider that inter-hemispheric balance is disrupted after stroke, interfering with recovery. UL motor function depends on the modulation of inter-hemispheric inhibition between cortical areas via transcallosal projections [9, 10] and descending projections to fingers, hand and arm [11]. Unilateral hemispheric damage reduces activity in the affected hemisphere while activity in the unaffected hemisphere increases [12], becoming more dominant. UL recovery may relate to rebalancing of inter-hemispheric inhibition [13] using, for example, anodal transcranial direct current stimulation (a-tDCS) over the affected hemisphere [14, 15]. a-tDCS is considered a safe technique with transient adverse effects, such as slight scalp itching or tingling and/or mild headaches, that are not expected to impede the patient’s ability to participate in the training protocol [16].

The underlying idea of this proposal is that recovery of voluntary movement is tightly linked to the recovery of threshold control. We propose an intervention that combines current knowledge about motor learning and disorders in ST control. The intervention involves personalized UL reach training designed according to the spatial structure of motor deficits of an individual, with excitatory a-tDCS over the sensorimotor areas of the affected hemisphere.

## Methods

### Aim, design and setting

We hypothesize that in patients with sub-acute spastic hemiparesis after stroke, practice restricted to the active control zone (personalized training) combined with excitatory a-tDCS will improve control over the range of ST regulation in the elbow and improve UL kinematic and clinical performance measures compared to non-personalized training with a-tDCS and personalized training with sham-tDCS. We propose a single-blind, parallel, three-group, randomized controlled trial (RCT; allocation ratio 1:1:1) involving personalized therapeutic intervention to improve control over the range of regulation of STs with the application of excitatory a-tDCS, which, under generally facilitatory conditions (e.g., motivating patients with VR games), may strengthen remaining connections and help restore inter-hemispheric balance. The Standard Protocol Items: Recommendations for Interventional Trials (SPIRIT) flow diagram of study enrollment, interventions and assessments is shown in Fig. 2. In addition, the implementation of such training programs in a low-to-middle-income country will be investigated by including four academic rehabilitation centers in Canada, Israel and India.

**Fig. 2 Fig2:**
[figure not shown]
Schedule of enrollment, interventions and assessments. Standard Protocol Items: Recommendations for Interventional Trials (SPIRIT) flow diagram of study enrollment, interventions and assessments

### Participants and recruitment

Sixty people with sub-acute spastic hemiparesis after stroke will be recruited during their hospitalization in rehabilitation centers. In order to achieve adequate participant enrollment, constant chart review of newly admitted patients will be done. Individuals will be included if they have/are: (1) a stroke in the middle cerebral territory, confirmed by magnetic resonance imaging/computed tomography (MRI/CT), and medically stable; (2) aged 25–80 years; (3) in the sub-acute stage of stroke (3 weeks to 6 months post stroke); (4) arm paresis (2–6/7 on the Chedoke-McMaster Stroke Assessment arm score, CMSA [17]) and able to perform at least 30° elbow flexion and extension; (5) elbow flexor and/or extensor spasticity (>1 + out of 4 on the Modified Ashworth Scale, MAS [18, 19]); and (6) able to provide informed consent. Exclusion criteria are: (1) other major neurological or neuromuscular/orthopedic problems or pain interfering with results’ interpretation; (2) medical co-morbidities such as HIV/AIDS, etc.; (3) major cognitive deficits (˂ 20 on the Montreal Cognitive Assessment, MoCA [20]); (4) history of psychiatric disorders, alcohol or drug abuse, seizures, migraines, metal in the cranium, and cochlear and cardiac implants; (5) taking medications (e.g., anti-epileptic and psychoactive drugs) that could affect brain activity [21, 22]. Criteria for discontinuation include participant request or adverse events.

Eligibility will be established by a blinded research coordinator. Participants will provide informed consent and be allocated to one of three treatment groups (*n* = 20 per group) by permuted block randomization, balanced for age (25–50 years/51–80 years) and chronicity (3–12 weeks/13–24 weeks). Participants will receive a training and evaluation schedule, and participation will be monitored by the study coordinator, who will also provide reminders to attend scheduled activities. Travel expenses will be remunerated for follow-up visits.

The sample size is based on preliminary data showing that the mean change in elbow-flexor ST angle was 10° in stroke subjects with spasticity who underwent 2 weeks of transcutaneous electrical nerve stimulation treatment compared to 2° after sham stimulation (unpublished data). Considering an *α* level of 5% and a 95% power (effect size = 2.23) to detect differences using a mixed-design 3 × 3 analysis of variance (ANOVA) (G*Power 3.1.1), the minimal sample size is 13 subjects per group. Sample size was increased to 18 per group to have an equal number of subjects per group per site (six per group, per site). We will recruit 20 subjects per country overall considering a dropout rate of 10–15% for a final cohort of 60 subjects.

Prior to the start of recruitment of participants, standardized procedures will be established to ensure consistency across sites. Intervention therapists will receive training guidelines and evaluators will receive screening and clinical assessment documents. In addition, all team members directly involved in data collection will have face-to-face training on data collection protocols. Quarterly online meetings will be scheduled to maintain adherence to the protocols across sites.

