### Intervention

Participants will enroll in a 10-day training program over two consecutive weeks (5 days per week). Outcome evaluators, statistical analysts and care providers will be blind to group assignment but not the intervention therapists, given the nature of the intervention. Intervention therapists will receive allocation information from the study coordinator via coded email. Participants will be randomly allocated as follows: (group 1) personalized training (reaching within determined active control zones) and a-tDCS over the affected hemisphere; (group 2) non-personalized training (reaching in both spasticity and active control zones; full active ROM) and a-tDCS over the affected hemisphere; and (group 3) personalized training and sham-tDCS.

Prior to the reaching training, elbow-flexor STs in the hemiparetic arm will be determined in each participant to identify the active control zone, using the Montreal Stretch Reflex Threshold device (MSRT; [23] see below). For the personalized training groups (groups 1 and 3), elbow extension will be restricted to the active control range using a range-restriction elbow brace (Breg Inc., Carlsbad, CA, USA) blocking elbow extension beyond the permitted ST. Participants in the non-personalized training group will wear the brace, but elbow ROM will not be restricted. All participants will have partial arm-weight support with a sling during the training to avoid fatigue. Since a goal of the training is to increase isolated elbow extension, the sling will be placed so that the weight of the upper arm and shoulder is supported without restricting elbow movements. The support will be provided throughout the training sessions for all subjects so that training parameters are equivalent across groups and sites.

During reaching training, participants will sit on an armless chair and make discrete arm reaches towards targets displayed at various locations in the three-dimensional (3D) workspace with unrestrained trunk movement. Training will be guided by a physical or occupational therapist for 50 min (actual movement time) per day. Four interactive games from the Jintronix VR system (Montreal, QC, Canada) will be viewed on a large screen. Three activities will involve unimanual movement and one will involve a bimanual activity (Fig. 3). The total amount of movement time each training day will be recorded by the Jintronix system. Treatments will be matched for both duration and intensity across sites.

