### Study outcomes

Outcome measures will be documented before (Pre), after 10 days of intervention (Post) and 1 month after intervention end (Follow-up). Measures will be used to obtain an overall clinical profile of arm and hand impairment and function. Arm motor recovery will be evaluated at two levels of the International Classification of Function: Body Structure and Function (motor impairment) and Activity [27]. The primary outcome will be the ST angle and the ratio between the range of the biceps spasticity zone and the full biomechanical elbow-extension ROM.

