#### Assessment of spasticity and active control zones

Since active elbow extension (active control zone) is limited by the location of the ST in the angular range of the elbow, the ST angle of the elbow flexors (biceps brachii, BB) will be measured. This will allow us to determine the range of angles in which BB cannot be relaxed (spasticity zone) and the range in which reciprocal agonist/antagonist muscle activation is possible (active control zone). The ST angle will be defined using the MSRT, a portable clinical device consisting of a two-channel electromyography (EMG) system (Procomp 5, Thought Technology, Montreal, QC, Canada), an electrogoniometer (servo-type rotational-position potentiometer P2200; Novotechnik U.S. Inc., Southborough, MA, USA) and dedicated software implemented on a laptop computer (Fig. 4). The MSRT has moderate-to-good intra- and inter-evaluator reliability for the measurement of elbow spasticity in post-stroke participants [23].

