**Fig. 4 Fig4:**
[figure not shown]
Montreal Stretch Reflex Threshold (MSRT) device. The MSRT is a portable, clinical device consisting of a two-channel electromyography (EMG) system, an electrogoniometer and dedicated software implemented on a laptop computer

BB and triceps brachii (TB) EMG recordings will be obtained with surface electrodes (Ambu® Blue Sensor P, Ballerup, Denmark), from motor points indicated in the Surface ElectroMyoGraphy for the Non-Invasive Assessment of Muscles (SENIAM) guidelines [28]. EMG signals will be band-pass filtered (10–1000 Hz), amplified (×500) and sampled at 2048 samples/s. Seated participants will perform a maximal voluntary contraction of the elbow flexors to adjust EMG gain and initial elbow angle will be specified. Then, 20 stretches will be performed manually by stretching the elbow from flexion (approximately 50^o^) to full extension. Participants will be instructed to relax completely without assisting or resisting the angular displacement. Adequate rest (10 s) will be allowed between stretches to minimize effects of fatigue and muscle thixotropy [29]. Before each stretch, a randomly assigned speed, equally distributed between slow, moderate and fast velocities, will be indicated by an auditory signal from the MSRT to avoid the participant anticipating the upcoming stretch. Each evaluation will last for approximately 20 min. At the end of each stretch, MSRT identifies the angle at which the EMG begins, called the dynamic stretch reflex threshold (DSRT) [23]. At the completion of at least 20 correct stretches, a linear regression line is computed through the DSRTs on the angular velocity/displacement plot from which the correlation coefficient (*r*^2^), slope and x-axis intercept are determined. The x-axis intercept corresponds to the tonic stretch reflex threshold (TSRT) angle. A low TSRT angle corresponds to a high level of spasticity.

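### Inclusion criterion 5 admits patients with extensor-only spasticity, although the primary outcomes and the personalised brace limit rest on the elbow-flexor threshold

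*Protocol article*

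**What the plan says.** Under Participants and recruitment, criterion 5 requires "elbow flexor and/or extensor spasticity" with a MAS score above 1+. Either muscle group is enough.

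The rest of the design refers to the flexors:

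- **Primary outcomes.** The abstract states: "Main outcomes are elbow-flexor spatial threshold and ratio of spasticity zone to full elbow-extension range". Study outcomes names the ST angle and "the ratio between the range of the biceps spasticity zone and the full biomechanical elbow-extension ROM".
- **Measurement.** Under Assessment of spasticity and active control zones, "the ST angle of the elbow flexors (biceps brachii, BB) will be measured". The test stretches are made by "stretching the elbow from flexion" to full extension, which lengthens the flexors. No extensor threshold is described.
- **Intervention.** Before training, "elbow-flexor STs in the hemiparetic arm will be determined in each participant to identify the active control zone". In the two personalised arms the brace then works by "blocking elbow extension beyond the permitted ST". The non-personalised arm wears the same brace without restriction.
- **Randomisation.** Allocation is balanced for age and chronicity only.

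Nothing in the article requires a flexor ST inside the joint range at entry.

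**The concern.** Entry is defined on either muscle group, while treatment and outcome are defined on one. A patient with qualifying extensor spasticity and no flexor spasticity would have nothing for the personalised brace to restrict and no biceps spasticity zone to reduce.

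The comparison most exposed is personalised training with a-tDCS against non-personalised training with a-tDCS, because these arms differ only in the restriction. The analysis follows intention to treat, so such patients stay in and pull the estimated difference towards zero. The floor on the ratio outcome also touches the a-tDCS versus sham comparison, since it limits improvement in any arm.

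**Working it through.** **Step 1: what happens to an extensor-only patient.** The Background and the Fig. 1 legend say that post-stroke spasticity arises when the threshold lies within the biomechanical range. In healthy subjects the relaxed threshold lies outside it. Criterion 5 is a MAS cut-off, not a threshold test, so a patient who qualifies on the extensors can have flexor MAS 0, 1 or 1+. There are two cases:

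| Flexor ST | Brace in personalised arms | Game calibration | Ratio outcome |
|---|---|---|---|
| Outside joint range | Restricts nothing | Active zone equals full active ROM | Starts at 0 |
| Inside range (mild flexor spasticity) | Restricts some extension | Differs between arms | Above 0, can fall |

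The first case removes the training contrast. The second leaves part of it.

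**Step 2: the plan's own sample-size figure.** Inputs from Participants and recruitment: ST change of 10° versus 2° (difference 8°), effect size 2.23, α 5%, power 95%, minimum 13 per group, raised to 18. If 2.23 is a standardised mean difference, the implied SD is 8/2.23 = 3.59°. A two-sided t-test at d = 2.23 reaches 95% power with 7 per group. The one-way and repeated-measures ANOVA variants tried with this effect size need 2 to 8 per group. The stated 13 was not reproduced. That is a separate matter and does not bear on this point. The 18 per group is used below.

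**Step 3: dilution.** Let p be the share of patients with no contrast at all. The documents give no value, so p is an assumption. The expected difference is multiplied by 1 − p, which is a loss of 10% at p = 10% and 20% at p = 20%. With SD held fixed, the sample-size multiplier is 1/(1 − p)²: 1/0.81 = 1.23 and 1/0.64 = 1.56.

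**Step 4: power at 18 per group** (two-sided 5% t-test, one pairwise comparison, noncentral t).

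*On the plan's effect size.* Mixing responders and non-responders also widens the spread in the personalised arm, so the pooled SD becomes √(3.59² + p(1 − p)·8²/2). At p = 20% this is √(12.87 + 5.12) = 4.24°, so d = 6.4/4.24 = 1.51.

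| p | Diluted d | Power |
|---|---|---|
| 0 | 2.23 | >99.9% |
| 10% | 1.81 | >99.9% |
| 20% | 1.51 | 99% |
| 30% | 1.27 | 96% |
| 50% | 0.88 | 72% |

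A simulation of 20,000 trials per row agrees: 99% at p = 20%, 95% at 30% and 72% at 50%.

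*On a smaller true effect, assumed d = 1.0, SD held fixed.*

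| p | Diluted d | Power |
|---|---|---|
| 0 | 1.0 | 83% |
| 10% | 0.9 | 75% |
| 20% | 0.8 | 65% |
| 30% | 0.7 | 53% |

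**The case against.** Much of the case against a stronger claim stands.

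- **A reader might infer that every extensor-only patient has a flexor ST out of range.** The documents do not say so. The Fig. 1 legend makes that statement about healthy subjects, and says only that the threshold may lie within the range after stroke. Flexor MAS 1 or 1+ falls short of the cut-off but is compatible with an in-range ST. The article itself rates MAS inter-rater reliability as poor to good, so a low flexor score does not prove a zero spasticity zone.
- **A reader might infer that these patients cannot respond on either primary outcome.** The floor is shown for the ratio only. The ST angle is a regression intercept, and the article treats values outside the joint range as meaningful.
- **A reader might apply the planning difference of 8° to this comparison.** It comes from electrical nerve stimulation against sham, not from personalised against non-personalised training. The 8° enters the working only to show how the plan's own effect size behaves under dilution.
- **A reader might conclude that the trial is underpowered.** On the stated effect size it is not, unless the share is large: power drops below 95% only at p of about 30%, and below 80% at about 46%. A material loss needs a smaller true effect, which is an assumption here.
- **Unseen screening documents may narrow the criterion in practice.** The article mentions that evaluators receive them. That is possible, but it does not change the published wording.

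None of this removes the mismatch between who may enter and what is treated and measured.

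**Conclusion.** The mismatch is in the text: extensor-only spasticity is sufficient for entry, while both primary outcomes and the personalisation depend on the flexor threshold. The full consequence (no training contrast, ratio at its floor) holds only for patients whose flexor ST lies outside the joint range. For those with mild flexor spasticity it is partial.

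The size is unknown because the share of such patients is not given, and there is no harm if none enrol. Power on the stated effect size is robust to a moderate share. It is not robust if the true difference between two active a-tDCS arms is nearer d = 1.0. At any power, the estimated effect is pulled towards zero in proportion to p. The figures assume no contrast at all in the share p, and those for d = 1.0 also hold the SD fixed. This should be corrected, but it does not invalidate the trial.

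**What to change.** Reconcile criterion 5 with the primary outcomes: require elbow-flexor spasticity at the existing MAS cut-off and allow extensor spasticity in addition. This is a wording amendment, and its cost is the loss of a few otherwise eligible patients.

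For patients already enrolled, add a sensitivity analysis restricted to those whose baseline flexor ST lies inside the biomechanical range, using the planned baseline measurement with the Montreal Stretch Reflex Threshold device (MSRT). The restriction rests on a baseline variable, so the comparison between arms remains randomised. The cost is a smaller sample in that analysis.

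Using the MSRT as an entry test before randomisation is optional. The article places the measurement before training and the baseline assessment at randomisation, so an entry test would add a procedure of about 20 minutes, with at least 20 correct stretches, to screening.

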### Statistical analyses

Descriptive statistics will be used to highlight main demographic and clinical characteristics of participants. After verification for linearity, normality and homoscedasticity, parametric mixed-model ANOVAs will be used to determine which stimulation and practice modality combinations lead to greater improvements. The mixed-model analysis will include one between-subject factor – group with three levels (personalized training + a-tDCS, non-personalized training + a-tDCS and personalized training + sham-tDCS), and one within-subject factor – time with three levels (Pre, Post and Follow-up). Multiple linear regression analyses on pooled data will identify relationships between primary outcomes and changes in clinical and kinematic measures. If assumptions for parametric tests are not met, non-parametric tests will be substituted. Results will be analyzed based on intention-to-treat principles. Individual participation in other in-patient services will be documented (physiotherapy, occupational therapy, speech therapy, social work, recreation, other) and compared between sites to account for effects of usual-care exposure. Results will be disseminated to individuals, user groups, health care and research professionals at trial completion.

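### The sample was raised to give equal arms per site, but site is neither a stated balancing factor nor a model term, and the two stated balancing factors are also left out of the model

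*Protocol article*

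**What the plan says.** All references are to the Methods of the protocol article.

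- **Sample size (Participants and recruitment).** The calculated minimum is 13 per group. It is raised to 18 "to have an equal number of subjects per group per site (six per group, per site"). The next sentence changes unit and plans 20 patients per country, 60 in all, allowing for 10–15% dropout.
- **Allocation (same section).** Participants are assigned to three arms "by permuted block randomization, balanced for age (25–50 years/51–80 years) and chronicity (3–12 weeks/13–24 weeks"). No other factor is named.
- **Setting (Aim, design and setting).** The trial is run by "including four academic rehabilitation centers in Canada, Israel and India".
- **Analysis (Statistical analyses).** "The mixed-model analysis will include one between-subject factor – group with three levels", together with one within-subject factor, time, at Pre, Post and Follow-up. Site appears in this section only in a between-site comparison of the other in-patient services that participants receive.

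**The concern.** Three statements that should fit together do not. Equal arms per site is the only reason given for five more patients per group. The allocation method, as described, does nothing to produce that equality. The analysis then uses neither site nor the two factors that the allocation does control.

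The choice matters because site differences in recovery are plausible here. The primary outcome comes from stretches applied by hand. The Modified Ashworth Scale is described as having poor-to-good inter-rater reliability. Patients are sub-acute in-patients in three countries, and the article itself plans to compare their usual care between sites. If sites, age bands or chronicity bands differ in how much patients change, uneven arms disturb the comparison in the trial actually run. Leaving these factors out of the model also leaves their effect on change in the error term.

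**Working it through.** **1. The plan's own arithmetic.** Inputs: six per group per site, 18 per group, 60 recruited, 10–15% dropout.

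- Implied number of sites: 18/6 = 3.
- Completers: 18 × 3 groups = 54.
- Recruitment at 10% dropout: 54/(1 − 0.10) = 60, which matches the plan. At 15% it is 54/(1 − 0.15) = 63.5, so 64.

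The figures reproduce if site means country. If site means centre, there are four: 18/4 = 4.5 per group per site, and six per cell would need 6 × 3 × 4 = 72 completers.

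**2. What the stated allocation delivers per country.** Assumptions, since the article gives no block size or list structure:

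- 60 patients, 20 per country, arriving in random order;
- one central list stratified by age × chronicity (four equally likely strata) that ignores country;
- permuted blocks of 3 or 6;
- 10,000 to 20,000 simulated trials per run.

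| Result | Simulated value |
|---|---|
| Mean of the largest within-country difference between arms | about 5.0 |
| Largest difference 4 or more | about 80% of trials |
| Largest difference 5 or more | 56–59% |
| All nine country-by-arm cells at least 6 | about 5% |
| Closest possible split (6/7/7) in every country | 1–2% |

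Block size makes little difference. These counts are at randomisation, before dropout.

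**3. Which adjustment reaches the test of interest.** Whether one arm improves more is tested by group × time. Write the outcome of patient i at visit t as y(i,t) = site offset + remainder. The group × time contrast uses y(i,t) minus the patient's own mean over visits, so an offset that is the same at all three visits cancels. A numerical check agrees: adding site offsets of any size to all three visits leaves the group × time F unchanged. The same holds for main effects of age band and chronicity band. Only differences in *change* matter. They are captured by factor × time terms, or by modelling Post and Follow-up with the Pre value as covariate and these factors included.

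**4. Cost in degrees of freedom.**

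- Baseline-adjusted model: centre 4 − 1 = 3, age band 1, chronicity band 1, total 5 (4 if country is used).
- Factor × time terms: each is multiplied by 3 − 1 = 2 for time, so 5 × 2 = 10 (8 with country). The within-subject error has (60 − 3) × 2 = 114 before this and 104 after.

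**5. Why blocks within every stratum would not work.** Site × age × chronicity gives 3 × 2 × 2 = 12 strata for countries (60/12 = 5 patients each) or 4 × 2 × 2 = 16 for centres (60/16 = 3.75 each). Many blocks would stay incomplete.

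**The case against.** **The article is condensed.** Separate lists per site may exist; permuted blocks are compatible with them, and the stated aim points that way. This stands in part: the simulation applies only if site is ignored. But the article names its balancing factors and states its model terms in full, and site is in neither. This is a specification as written, not a detail passed over.

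**Three sites against four centres.** A reader might infer an arithmetic error. The documents do not support that. The text moves straight from six per site to 20 per country, and with site read as country the sums close (54/0.90 = 60). What remains is an undefined term. That 20 does not divide by three is no fault either, since 20 includes the dropout allowance and 18 divides evenly.

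**Bias and confounding.** A reader might also infer that arm is confounded with site. It is not: allocation that ignores site gives imbalance by chance, with zero expected bias. Evaluators are blinded, procedures and training are standardised, treatment is matched across sites and usual care is documented. These safeguards reduce site differences, but they neither balance the arms within sites nor adjust any treatment estimate.

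**Gain from a site term.** It is tempting to say that adding site would remove a given share of residual variance. The documents contain no figure for site variance, and a site main effect does not change the group × time test at all. Any gain depends on how far these factors predict change, which is unknown.

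**Conclusion.** The point holds as a mismatch between a declared design aim, the stated allocation and the stated model. With country as the unit and allocation blind to it, six per group in every country is reached in about 5% of trials, and an arm difference of 4 or more in at least one country occurs in about 80%. These figures rest on one central list, 20 per country and equally likely strata. The consequence is chance imbalance and some loss of precision, and only so far as site, age or chronicity predict change in the outcome. The size of that loss cannot be derived from the article. This is a worthwhile, inexpensive improvement and not a threat to the trial's validity.

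**What to change.** 1. **Analysis.** In the primary and secondary models, adjust the change over time for site (or country), age band and chronicity band. Use either factor × time terms in the mixed model or a baseline-adjusted model of Post and Follow-up that includes these factors. Main effects alone are not enough. This can be done whatever has already been recruited, and costs about 5 degrees of freedom in the baseline-adjusted model or about 10 with the time interactions.
2. **Allocation.** For any participants still to be enrolled (recruitment was planned to December 2018), allocate within site or country. Minimisation with a random element on site, age band and chronicity band is one suitable method, because 12 to 16 strata are too fine for blocks with 60 patients. The cost is a change to the allocation procedure. If separate lists per site are already in use, saying so is sufficient.
3. **Text.** In the sample-size paragraph, state whether site means country or centre, and reword the six-per-group statement to match. With country it stands as 3 × 6 = 18; with four centres it cannot stand at 18 per group. This costs only an edit.
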